### Sample size calculation

The 2016 paper by Gandler et al. found a pre-operative dietitian intervention before TJA resulted in a weight loss of − 3.38 kg (standard deviation [SD] 6.62) versus a weight gain of + 2.01 kg (SD 6.45) in the usual care group [13]. Using 80% power to detect a difference between weight loss of − 3.38 kg in the intervention group versus + 2.01 kg weight gain in the usual care group with SD 6.62 kg, this study would require 24 patients per arm. Thus, we will aim for 30 participants in each arm to allow for 25% dropout.

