### Randomization and allocation

Enrolled subjects will be randomized into two groups with an allocation ratio of 1:1 in blocks of four. The allocation table will be randomly generated via Microsoft Excel by an independent third-party clinical researcher, uploaded to the study REDCap randomization model, and will not be accessible to study staff within REDCap. Group assignment will be revealed via the REDCap model only at the time of randomization during enrollment following informed consent procedures and enrollment BMI verification.

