### Statistical analyses

The main statistical analysis will be performed via an intention-to-treat analysis. Per protocol sensitivity analysis (completing at least half or four video calls) will also be performed. The significance level for statistical tests will be set at *p* ≤ 0.05. Baseline characteristics between the two groups will be assessed using t-tests for continuous variables and chi-square or two-tailed Fisher’s exact tests (when required by small cell counts) for categorical variables. Differences over time in continuous variables between the intervention and clinical standard of care group, such as percent weight change, body weight, and BMI, will be analyzed using *t* tests. Missing week 12 weight outcomes will be carried forward from week 6 outcomes when available.

We will measure feasibility via the ease of recruitment based on the ratio of enrolled subjects to the number of people approached about the study, and via maintenance of contact with a dietitian (e.g., number of video calls completed) based on study participant attrition and follow-up survey completion rates (retention). We will measure acceptability via survey items about components of the intervention, and through qualitative comments from a semi-structured interview. We will perform survey analyses using SAS (SAS Institute Inc., Cary, NC) or similar software. For most questions, participants will choose between four categories: strongly agree, somewhat agree, somewhat disagree, and strongly disagree. Assuming the distribution of responses to baseline surveys will be relatively similar, we will pool follow-up survey answers into “agree” and “disagree” for simplicity, and then conduct chi-square or two-tailed Fisher’s exact tests to examine differences between intervention and control group responses to follow-up surveys.

Qualitative data will be analyzed using the immersion crystallization method [29]. This qualitative technique includes multiple rounds of “immersion” through close readings of transcripts, followed by reflection and the “crystallization” of emerging themes. Multiple investigators will read the transcripts and arrive at a unanimous consensus concerning the emerging themes. Then, one investigator will code the transcripts to organize representative quotes.

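### Thirty patients per arm absorbs 20% dropout, not the stated 25%, because 24 was multiplied by 1.25 rather than divided by 0.75 (minor)

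*Protocol article*

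**What the plan says.** Under Sample size calculation, the protocol article takes the weight changes of an earlier randomised study of a dietitian intervention around joint replacement: "3.38 kg in the intervention group versus + 2.01 kg weight gain in the usual care group with SD 6.62 kg". It sets the target as "Using 80% power to detect a difference" and concludes that "this study would require 24 patients per arm". The enrolment figure follows: "Thus, we will aim for 30 participants in each arm to allow for 25% dropout". The abstract gives the matching total of 60.

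Three other statements bear on the check:

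- Under Randomization and allocation, patients are "randomized into two groups with an allocation ratio of 1:1 in blocks of four".
- Under Statistical analyses, the level is fixed: "The significance level for statistical tests will be set at *p* ≤ 0.05". Continuous outcomes such as body weight "will be analyzed using *t* tests".
- The same section makes intention-to-treat the main analysis. It fills a missing week 12 weight with the week 6 weight if there is one.

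The article nowhere gives the 25% a meaning other than the share of enrolled patients who are lost.

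**The concern.** Dropout is a fraction of the patients enrolled, so the number left is the number enrolled times one minus that fraction. The article instead adds 25% to the number required. These are different operations, and the second always gives too small an allowance. As a result, three stated figures cannot all hold: 24 analysed per arm, 30 enrolled per arm, and a tolerance of 25% loss.

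At stake is the accuracy of the sample-size statement for the primary outcome. Attrition is also one of the trial's feasibility measures, so readers will probably set the observed dropout beside the stated allowance. A loss between 20% and 25% would look as if it had been provided for when it had not.

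**Working it through.** **Inputs**

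- Difference: 3.38 + 2.01 = 5.39 kg (Sample size calculation).
- SD: 6.62 kg in both arms (same section).
- Power 80% (same section); alpha 0.05 (Statistical analyses); allocation 1:1 (Randomization and allocation).
- Sidedness: not stated for the t-test. Two-sided is assumed, because it reproduces the 24; a one-sided test would need 19.

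**Step 1: reproduce the 24**

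Normal approximation, per arm:

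n = 2 × (1.960 + 0.842)² × (6.62 / 5.39)² = 23.68, rounded up to 24.

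This matches the article. The same calculation with the t distribution gives 24.68, rounded up to 25.

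**Step 2: the dropout allowance**

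- What the article appears to have done: 24 × 1.25 = 30.
- What a 25% loss requires: 24 / (1 − 0.25) = 32 per arm, 64 in total.
- Left from 30 after 25% loss: 30 × 0.75 = 22.5, so 22 or 23 per arm.
- Largest loss that leaves 24 of 30: 1 − 24/30 = 20%, or 6 patients per arm.

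The gap is 2 patients per arm, 4 in total.

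**Step 3: power at the numbers left**

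Normal approximation: power = Φ(5.39 / (6.62 × √(2/n)) − 1.960). For n = 22.5 this is Φ(2.731 − 1.960) = Φ(0.771) = 78.0%. The t-test column uses the noncentral t distribution.

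| Analysed per arm | Normal approximation | t-test |
|---|---|---|
| 22 | 77.0% | 75.1% |
| 22.5 | 78.0% | 76.1% |
| 23 | 78.8% | 77.0% |
| 24 | 80.5% | 78.8% |
| 25 | 82.1% | 80.5% |
| 30 (no loss) | 88.4% | 87.3% |

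**Step 4: the same statement on the t-test basis**

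If 25 per arm are required, 30 per arm absorbs 1 − 25/30 = 16.7%, about 17%.

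**The case against.** The arithmetic of the allowance is hard to dispute, but there is a good case against making much of it.

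*Not every dropout leaves the analysis.* The week 6 weight is carried forward when week 12 is missing, and every participant is paid for verifying a week 6 weight. To fall below 24 analysed, an arm would need more than 6 patients with neither weight. This stands, and it is why the power figures above are conditional. It does not rescue the sentence. Carry-forward works only where a week 6 value exists, it may dilute the treatment difference, and the article does not use it to justify 30.

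*The 25% is a tolerance.* A reader might infer that the trial will miss its 24 per arm, or that the plan expects to. The document does not support that. It allows for 25% dropout without forecasting it, and at 20% or less the target is met.

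*The inputs are slightly conservative.* The larger of the two published SDs (6.62 rather than 6.45 kg) is applied to both arms. With the two pooled, √((6.62² + 6.45²)/2) = 6.54 kg, power at 22–23 per arm is 78.1–79.9% by the normal approximation and 76.2–78.1% by the t-test. This also stands. The shortfall shrinks but does not disappear.

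*24 rather than 25.* A reader might count this as a second error, since a t-test is planned and 24 gives 78.8%. It is a one-patient difference between two standard formulas. The article does not name its formula, and the 24 reproduces, so it is not an error in the plan. It matters only in that a corrected sentence must not mix the two methods.

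**Conclusion.** Wrong as written, minor in severity. Thirty per arm covers a 20% loss from the analysis, not 25%.

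If a full quarter of each arm had no analysable weight, power would be 1 to 3 percentage points below the stated 80% by the normal approximation, or 3 to 5 points below by the t-test. This rests on a two-sided 0.05 test, the article's own difference and SD, and dropout meaning that neither a week 12 nor a week 6 weight is available.

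The stronger conclusion, that the primary comparison is underpowered or that the trial must enlarge, does not follow. The shortfall arises only when more than 20% of an arm is unanalysed, and even then it is too small to undermine the comparison.

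**What to change.** Keep 60 patients and correct the sentence, using one method throughout. Either of these would do:

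- *Normal approximation, which reproduces the 24:* 30 per arm allows for 20% dropout; at 25% dropout (22–23 analysed per arm) power for a 5.39 kg difference is about 78%.
- *t-test:* 25 per arm are needed; 30 per arm allows for about 17% dropout; at 25% dropout power is about 76%.

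Pairing the 20% from the first with the 76% from the second would replace one inconsistency with another. It would help to add that the test is two-sided and that dropout here means having neither a week 12 nor a week 6 weight.

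The cost is one sentence and a slightly less favourable stated figure. Design, conduct and analysis do not change. If the sponsor prefers to keep the 25% tolerance, the alternative is 32 per arm (64 in total, on the normal approximation), at a cost of 4 more patients. The size of the shortfall does not require it.

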### Statistical analyses

The main statistical analysis will be performed via an intention-to-treat analysis. Per protocol sensitivity analysis (completing at least half or four video calls) will also be performed. The significance level for statistical tests will be set at *p* ≤ 0.05. Baseline characteristics between the two groups will be assessed using t-tests for continuous variables and chi-square or two-tailed Fisher’s exact tests (when required by small cell counts) for categorical variables. Differences over time in continuous variables between the intervention and clinical standard of care group, such as percent weight change, body weight, and BMI, will be analyzed using *t* tests. Missing week 12 weight outcomes will be carried forward from week 6 outcomes when available.

We will measure feasibility via the ease of recruitment based on the ratio of enrolled subjects to the number of people approached about the study, and via maintenance of contact with a dietitian (e.g., number of video calls completed) based on study participant attrition and follow-up survey completion rates (retention). We will measure acceptability via survey items about components of the intervention, and through qualitative comments from a semi-structured interview. We will perform survey analyses using SAS (SAS Institute Inc., Cary, NC) or similar software. For most questions, participants will choose between four categories: strongly agree, somewhat agree, somewhat disagree, and strongly disagree. Assuming the distribution of responses to baseline surveys will be relatively similar, we will pool follow-up survey answers into “agree” and “disagree” for simplicity, and then conduct chi-square or two-tailed Fisher’s exact tests to examine differences between intervention and control group responses to follow-up surveys.

Qualitative data will be analyzed using the immersion crystallization method [29]. This qualitative technique includes multiple rounds of “immersion” through close readings of transcripts, followed by reflection and the “crystallization” of emerging themes. Multiple investigators will read the transcripts and arrive at a unanimous consensus concerning the emerging themes. Then, one investigator will code the transcripts to organize representative quotes.

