### Arms

Intervention participants will download a telemedicine online/smartphone app (Nutrimedy, Brookline, MA, USA) and be connected at enrollment with a certified registered dietitian who will contact intervention participants weekly or bi-weekly via video calls and unlimited in-app text messaging for up to 3 months. The first week will include either one 55-min video session or two 25-min sessions. Weeks 2–4 will have weekly 25-min video calls, and weeks 5–12 will have biweekly 25-min sessions for a total of 8–9 sessions over 12 weeks. Together, participants and dietitians will come up with goals for the 12 weeks, and dietitians will check on progress toward these goals using in-app tools such as food logs and messaging between video calls. All patients will be encouraged to lose at least 20 pounds with a goal BMI < 40 kg/m^2^ after 12 weeks.

Dietitians will use principles of motivational interviewing, cognitive behavioral interventions, and the socioecological model to remotely provide behavior and lifestyle interventions. Motivational interviewing is a patient-centered, collaborative approach to counseling in which the dietitian elicits personally relevant reasons from subjects to make behavior changes that may promote weight loss. Dietitians and patients then structures goals for lifestyle modifications around these personal motivations [17]. Cognitive behavioral interventions provide subjects with strategies to change cognitive processes to alter behaviors, such as self-monitoring (e.g., recording food intake, weight, and exercise), stimulus control (e.g., keeping less healthy foods in cabinets out of sight), and accountability by having frequent check-ins with dietitians [18]. The socioecological model proposes that multiple levels of influence including intrapersonal (e.g., knowledge and attitudes), interpersonal (e.g., family and friends), and community factors (e.g., organizations, workplaces, neighborhoods) can impact energy-balance behaviors and weight outcomes [19]. Dietitians will promote the adoption and maintenance of behaviors across multiple levels of influence.

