Individuals randomized to the clinical standard of care group will receive care according to current clinical guidelines. This may include a physical therapist and/or nutritionist referral, of which several programs within the institutions are offered to patients interested in weight loss, including the Nutrition Wellness Service (NWS) and Program for Weight Management (PWM).

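### The per-protocol analysis filters only the intervention arm on call attendance, so it can favour the intervention with no true effect and should not be read as confirming the intention-to-treat result

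*Protocol article*

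**What the plan says.** The Statistical analyses section of the Protocol article puts intention-to-treat first: "The main statistical analysis will be performed via an intention-to-treat analysis". It then adds: "Per protocol sensitivity analysis (completing at least half or four video calls) will also be performed". Continuous outcomes "such as percent weight change, body weight, and BMI, will be analyzed using" t tests, at a 0.05 significance level. No adjustment for predictors of attendance is stated. A missing week 12 weight is replaced by the week 6 weight where there is one.

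The Arms section gives the calls to one group only. The dietitian is to "contact intervention participants weekly or bi-weekly via video calls and unlimited in-app text messaging for up to 3 months". The first week has one long session or two short ones, weeks 2–4 have weekly calls, and weeks 5–12 have "biweekly 25-min sessions for a total of 8–9 sessions over 12 weeks". For the other group, "Individuals randomized to the clinical standard of care group will receive care according to current clinical guidelines", possibly with referrals. No attendance or adherence criterion is given for controls, and the article does not say how controls enter the per-protocol set.

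**The concern.** A criterion based on completed video calls cannot be applied to people who have no calls. As written, the per-protocol contrast sets intervention participants who chose to keep attending against an unselected control arm. That comparison no longer rests on randomisation. The protocol itself treats motivation as a driver of weight loss, and its surveys measure motivation, interest and confidence. Motivation may well drive attendance too. If so, the attenders would have lost more weight than the average participant without any help from the dietitian, and the contrast credits that to the intervention.

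A sensitivity analysis is normally read as a test of whether the main result is robust. This one changes who is compared, plausibly in a direction that flatters the main result, so agreement between the two would reassure less than it seems to.

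The threshold adds a smaller problem. Half and four are offered together but do not always coincide. With about 30 people in the arm, reclassifying a few of them could move the estimate.

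**Working it through.** **The plan's own figure.** The Sample size calculation section gives −3.38 kg versus +2.01 kg (difference 5.39 kg), SD 6.62 kg, 80% power and 24 per arm. Assuming a two-sided 5% test, n = 2 × (1.960 + 0.842)² × (6.62/5.39)² = 23.7, so 24. This reproduces; the exact t-test calculation gives 24.7. The article gives no figure for the per-protocol analysis, so the SD and the 5.39 kg serve only as a scale below.

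**Calls against the threshold (Arms section).**
- Due by the end of week 4: 1 + 3 = 4 (one long first session) or 2 + 3 = 5 (two short ones).
- Due over 12 weeks: 4 + 4 = 8 or 5 + 4 = 9.
- Half of 8 is 4. Half of 9 is 4.5, so five whole calls are needed. A participant with nine scheduled calls who completes exactly four meets one criterion and not the other.
- A participant who attends every call and stops at the end of week 4 has completed four or five, and so reaches four. If the week 12 weight is missing, that person can enter with a week 6 weight.

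**Bias with no true effect.** Neither input below is in the documents; both are assumptions, shown as ranges.
- p: the share of the intervention arm that meets the threshold, 60–90%.
- ρ: the correlation between the propensity to attend and the weight loss that would occur anyway.

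Let attendance propensity be standard normal, with completion when it exceeds c, where c = z(1−p). The mean propensity among completers is φ(c)/p. Their expected difference from unfiltered controls is −ρ × 6.62 × φ(c)/p kg (negative favours the intervention).

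| p | φ(c)/p | ρ = 0 | ρ = 0.2 | ρ = 0.3 | ρ = 0.5 |
|---|---|---|---|---|---|
| 60% | 0.644 | 0 | −0.85 | −1.28 | −2.13 |
| 70% | 0.497 | 0 | −0.66 | −0.99 | −1.64 |
| 80% | 0.350 | 0 | −0.46 | −0.70 | −1.16 |
| 90% | 0.195 | 0 | −0.26 | −0.39 | −0.65 |

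As a share of 5.39 kg, ρ = 0.2 gives 0.26/5.39 = 5% to 0.85/5.39 = 16%, and ρ = 0.3 gives 0.39/5.39 = 7% to 1.28/5.39 = 24%.

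**Simulation.** In 20,000 trials per setting, with 30 randomised per arm, no effect and all controls kept, the mean biases matched the table to within 0.03 kg. The chance of a significant result favouring the intervention (nominal 2.5%) was:
- ρ = 0: 2.4–2.6%
- ρ = 0.2: 3.6–6.4%
- ρ = 0.3: 4.1–9.3%
- ρ = 0.5: 5.2–18.3%

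The chance that the point estimate merely favoured the intervention was about 50% at ρ = 0 and 58–75% at ρ = 0.3.

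**The alternative estimator.** With one arm having no access to calls, the complier-average effect is the intention-to-treat difference divided by p. If no participant is affected, the numerator is centred on zero and so is the estimate, whatever ρ is. If participants below the threshold have an average effect d, the estimate is the true complier effect plus d × (1−p)/p. At p = 70% that adds 0.43 × d.

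Approximate standard errors at p = 70%, if all weights are observed and without the gain from baseline weight:
- attenders versus controls (21 versus 30): 6.62 × √(1/21 + 1/30) = 1.88 kg
- complier-average: 6.62 × √(2/30) / 0.70 = 1.71/0.70 = 2.44 kg

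**The case against.** The strongest reply is that nothing decisive rests on this analysis. Intention-to-treat comes first, the per-protocol analysis is labelled a sensitivity analysis, and the article nowhere says it will support an efficacy claim. The weakness is common to adherence-based analyses with an untreated control. The bias is also modest beside the noise: at 70% completion, 0.66–0.99 kg is 0.35–0.53 of the 1.88 kg standard error. All of this stands, and it limits the weight of the point. It does not make the contrast a fair check on the main result.

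On the threshold, calls are front-loaded by design, and the ninth exists only because the first session may be split. The trial used for the sample size also had a minimum of four sessions. So four is not arbitrary, and the half-or-four mismatch is a matter of wording, though one that can change who is counted. A reader might infer that the threshold must be raised beyond what week 4 allows. The documents do not require that, and under the model above a stricter threshold (smaller p) increases the selection bias in the attenders-only contrast.

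A further objection is to the remedy. Intervention participants also have the app, food logs and unlimited messaging, and someone who completes three calls has still been counselled. This strains the assumption that randomisation acts only through reaching the threshold. The objection stands, and is why the complier-average effect should be supportive only.

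Finally, how controls enter the per-protocol set is inferred. The article is silent, but the criterion as written cannot filter them.

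**Conclusion.** The point holds as a caution about a secondary analysis. The per-protocol contrast filters one arm on a post-randomisation behaviour and can favour the intervention with no true effect, by about 0.3–0.9 kg at ρ = 0.2 and 0.4–1.3 kg at ρ = 0.3 for completion of 60–90%. These sizes depend on an assumed completion rate and an assumed correlation. That the rule cannot filter controls, that four calls can be reached by week 4, and that half and four differ for nine sessions follow from the text alone.

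Two stronger readings are tempting. One is that the analysis will show a benefit even if the intervention does nothing. The documents do not support this: the bias is zero if attendance is unrelated to weight change, could reverse if successful participants stop calling, and even at ρ = 0.5 gives a significant false benefit in at most about 18% of trials. The other is that this is the trial's only planned sensitivity analysis. It is the only one this article labels as such, but the article is condensed and a fuller plan may hold others.

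The primary intention-to-treat inference is unaffected.

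**What to change.** 1. Report the attenders-only result descriptively, without a confirmatory p-value, and say that it does not confirm the intention-to-treat result.
2. Make the adherence analysis a supportive complier-average effect that keeps all randomised participants in both arms: two-stage least squares for 12-week weight change, with randomised arm as the instrument for meeting the threshold and baseline weight as covariate.
3. State the exclusion assumption beside the estimate, and that the app, food logs, messaging and partial call attendance may violate it.
4. Fix one unambiguous threshold before unblinding, either a number of calls or a share of scheduled calls with a rounding rule. Note that four calls can be reached by week 4.

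The change is to analysis wording and needs no new data. The cost is a wider interval (standard error about 2.4 kg against 1.9 kg at 70% completion). If participants below the threshold also benefit, the complier effect is overstated. It remains centred on zero when the intervention has no effect, which the attenders-only contrast does not if attendance and weight change are related.

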### Patient population and recruitment procedure

Patients of fellowship trained arthroplasty surgeons at two institutions will be identified as potentially eligible for the study based on 40 kg/m^2^ < BMI < 47 kg/m^2^ recorded in the patient’s medical record within the last 6 months and recommended primary, unilateral total knee or hip arthroplasty. For patients identified as potentially eligible while in clinic, an orthopaedic surgeon will introduce the patient to the study, and a member of the research team (research assistant or trainee) will conduct an eligibility screening and obtain verbal consent either in-person or by phone. For patients identified as potentially eligible outside of clinic, a member of the research team will call the patient to introduce the study, and conduct eligibility screening and consent on the phone.

Eligible, interested, and consented patients will be provisionally enrolled, and all subjects will be shipped a standard bathroom scale to their home (Fig. 1). This initial enrollment is provisional, as subjects will be required to verify enrollment BMI by (a) submitting a photo to the study team of their study scale during a weigh-in that displays their body weight, or by (b) recording a baseline weight at an onsite healthcare facility within 2 weeks of provisional enrollment. Once enrollment BMI is verified to be 40 to 47 kg/m^2^, subjects will be fully enrolled and randomized to the intervention arm or clinical standard of care arm via REDCap. Subjects will be given a $40 check for enrolling, which includes (1) taking a baseline survey, (2) recording the baseline weight at an onsite healthcare facility or with a home study scale, and (3) getting baseline labs within 2 weeks of the baseline weight. Baseline weights will be recorded without shoes or outer clothing (e.g., coats). All subjects will be given a $20 check if they can verify a mid-study weight during week 6 of the study by recording a weight at any onsite healthcare facility or by submitting home study scale photos. All subjects will receive a $40 check for completing an end-of-study survey, weight, and labs at 10–14 weeks after enrollment.

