### Surveys

All participants will complete a baseline survey at enrollment, and an end-of-study survey 10–14 weeks after enrollment (Additional files 1, 2 and 3). Questions about weight loss methods and the level of interest and confidence in weight loss were taken from Cleveland et al. [20]. Questions about motivation for weight loss were adapted from Meyer et al. [21]. Questions about exercise, diet, and goal setting routines were taken from the Paving Wheel Wellness score by Frates [22]. Items querying food frequency, hours spent doing physical activity, demographics, and opinions about the intervention were adopted from Seward et al. [8]. Alcohol and tobacco use questions were taken from the AUDIT-C alcohol screen and World Health Organization Global Tobacco Surveillance System [23, 24]. Surveys also included the Lower Extremity Activity Scale (LEAS) [25], PROMIS-Global Health scale, and the Knee injury and Osteoarthritis Outcome Score (KOOS) or Hip disability and Osteoarthritis Outcome Score (HOOS) depending on the joint [26, 27]. In addition to the demographic information collected on baseline surveys, we will also review each subject’s electronic medical record to obtain medication lists.

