#### Primary outcome measurement

The primary outcome will be weight change at 12 weeks (10–14 weeks) after study enrollment. Weights will be recorded at an onsite healthcare clinic or by home study scales.

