This study has the potential to deliver a higher quality pre-operative weight loss intervention for patients than previously studied interventions, as it provides accessible and convenient dietary advice that is offered on a one-on-one basis, at more frequent time intervals, on-demand, and commencing earlier prior to surgery compared to methods described in previous studies. This study offers individualized one-on-one sessions as opposed to the group sessions offered in the Liljensøe et al. study, provides an average of three sessions with a dietitian every 4 weeks compared to at least four sessions over 1 year in the Gandler et al. study, and begins 12 weeks before surgery compared to an average of 20 days before surgery in the Pellegrini et al. study [12–14].

Considering the COVID-19 physical distancing recommendations and clinic suspensions, this study can provide important lessons on remote weight monitoring and nutrition services. While we intend to collect baseline and end-of-study laboratory data on subjects, collecting labs at both timepoints may not ultimately be feasible due to COVID-19. Remote weight monitoring will be the primary challenge conducting this study and will require sending study scales to subjects’ homes to verify recorded weights. Future studies may benefit from exploring open source smart scales that can more easily integrate with third-party mobile apps, allowing for frequent, verified weight measurements without sacrificing convenience for study participants.

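### Continuous outcomes are compared by t tests on change with no baseline covariate; baseline-adjusted ANCOVA would help a little for weight and more for patient-reported scores

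*Protocol article*

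**What the plan says.** The primary outcome is defined as a change: "The primary outcome will be weight change at 12 weeks (10–14 weeks) after study enrollment" (Primary outcome measurement). The Statistical analyses section takes as the quantity to be compared "Differences over time in continuous variables between the intervention and clinical standard of care group", and continues "such as percent weight change, body weight, and BMI, will be analyzed using" t tests. No covariate or adjusted model appears there.

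Baseline has one other use in that section for continuous variables: "Baseline characteristics between the two groups will be assessed using t-tests for continuous variables". Nothing is said to follow from the result of those tests.

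Baseline data are collected early. On weight, the recruitment section says "Once enrollment BMI is verified to be 40 to 47 kg/m^2^, subjects will be fully enrolled and randomized". The Surveys section, which covers PROMIS, KOOS/HOOS and LEAS, says "All participants will complete a baseline survey at enrollment, and an end-of-study survey 10–14 weeks after enrollment". Labs are less certain; the Discussion warns that "collecting labs at both timepoints may not ultimately be feasible due to COVID-19".

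On allocation, the article says "Enrolled subjects will be randomized into two groups with an allocation ratio of 1:1 in blocks of four" and mentions no stratification factor.

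**The concern.** In a trial of 60 patients sized at 24 evaluable per arm, precision is scarce and some chance imbalance at baseline is to be expected. Subtracting baseline fixes its coefficient at 1. When follow-up depends on baseline with a slope below 1, that over-subtracts: it adds noise, and an arm that happens to start heavier will on average show more apparent loss. ANCOVA estimates the slope instead. At stake are some efficiency and a conditional bias, which could be reduced with data already being collected. If adjustment is not fixed in advance, it may also be decided after the planned baseline tests have been seen.

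**Working it through.** **Inputs from the article (Sample size calculation).** Changes of −3.38 kg and +2.01 kg, so a difference of 5.39 kg; SD of change 6.62 kg; 80% power; 24 per arm, raised to 30. Alpha is 0.05 (Statistical analyses). The sidedness of the t tests is not stated.

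**The plan's own figure.** n per arm = 2 × [6.62 × (1.960 + 0.842) / 5.39]² = 23.7, so 24. The figure reproduces as a two-sided, unadjusted comparison of change (one-sided would give 19). With the exact t distribution, power at 24 per arm is 0.788.

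**Assumptions.** The article gives neither a baseline weight SD nor a baseline-to-follow-up correlation. I take a baseline SD s of 8 to 20 kg, the same SD at week 12, and hold the SD of change at 6.62 kg.

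**Formulas.**
- Variance of change = 2s²(1 − ρ) = 6.62², so ρ = 1 − 6.62²/(2s²).
- ANCOVA residual variance = s²(1 − ρ²).
- Ratio of ANCOVA to change-score variance = (1 − ρ²)/[2(1 − ρ)] = (1 + ρ)/2.
- One standard error of the difference in baseline means at 30 per arm = s√(2/30). The bias this leaves in a change-score comparison = (1 − ρ) × s√(2/30).

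Example, s = 15: ρ = 1 − 43.82/450 = 0.903; ratio = 1.903/2 = 0.951; imbalance = 15 × 0.258 = 3.87 kg; remaining bias = 0.097 × 3.87 = 0.38 kg.

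| s (kg) | ρ | Variance ratio | n per arm for 80% power (normal approximation) | Remaining bias (kg) | ANCOVA power at 24 per arm, simulated |
|---|---|---|---|---|---|
| 8 | 0.66 | 0.83 | 20 | 0.71 | about 0.85 |
| 10 | 0.78 | 0.89 | 22 | 0.57 | 0.82 |
| 15 | 0.90 | 0.95 | 23 | 0.38 | 0.80 |
| 20 | 0.95 | 0.97 | 24 | 0.28 | about 0.79 |

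The simulated power of the change-score t test is about 0.79 in every row. The ANCOVA column has baseline as the only covariate.

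**When equal variances fail.** In general the asymptotic gain is the squared correlation between change and baseline. Under equal variances that is (1 − ρ)/2. If change is unrelated to baseline, the gain is zero and the degree of freedom is wasted: simulated power at 24 per arm drops by about one point from 0.79.

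**Other continuous outcomes.** With assumed ρ of 0.3, 0.5 and 0.7, (1 + ρ)/2 is 0.65, 0.75 and 0.85, a variance reduction of 35%, 25% and 15%. At ρ = 0.5 that is worth 1/0.75 = 1.33 times the sample size.

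**The case against.** The strongest defence is that the plan is sound as written. A t test on change is unbiased over randomization and matches the basis of the sample size, which reproduces. Two stronger readings should be set aside:

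- *Baseline imbalance is left uncorrected.* A reader might infer this from the missing covariate. The outcome is a change score, so baseline is already subtracted. What remains is 0.3 to 0.7 kg against a design difference of 5.39 kg (0.28/5.39 = 5% to 0.71/5.39 = 13%).
- *Raw week-12 weight is compared.* The list of examples includes body weight and BMI as levels, and such a comparison would have power of only 0.15 to 0.63 at 24 per arm. But the sentence opens with "Differences over time in continuous variables between the intervention and clinical standard of care group", so change is what is meant. At most the wording could be tightened.

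The defence is also right that the gain on weight is fragile. Entry is restricted to BMI 40 to 47 and follow-up is not, so equal variances are doubtful. Adding site as well as baseline, with site not prognostic, removes the gain at the larger SDs: simulated power is 0.791 for both methods at SD 15 kg, and 0.788 for the t test against 0.784 at SD 20 kg. If change is also unrelated to baseline, the figures are 0.786 and 0.767. So adjustment is not free, and site should not be added by default. Nor does the article's silence on stratification show that there is none, since an article may leave that to the full protocol.

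PROMIS, KOOS/HOOS and labs are not named in the t-test sentence. They come under it because it speaks of continuous variables and lists examples only. Baseline labs are not assured for everyone, though a change score needs the baseline value too.

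What stands against the plan is that it does name a method, unadjusted t tests, so this is a stated choice and not a detail left open. A better method uses data the trial already intends to collect.

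**Conclusion.** The point holds as a modest matter of efficiency and conditional bias. It is not an invalid test or an error in the plan. For the primary outcome, baseline adjustment lowers variance by about 3 to 17% and moves power at 24 per arm from 0.79 to about 0.79 to 0.85, with the low end applying when weights are very highly correlated. The clearer benefit is for moderately correlated outcomes such as PROMIS and KOOS/HOOS, where variance falls by about 15 to 35%.

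These sizes rest on an assumed baseline SD of 8 to 20 kg, assumed correlations of 0.3 to 0.7 for the scores, and equal variances at baseline and follow-up. None of these is given in the article. If change in weight is unrelated to baseline, the primary comparison loses about one point of power. The documents do not support a claim that the primary analysis is seriously underpowered, or left exposed to baseline imbalance, because of this choice.

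**What to change.** Before unblinding, replace the t-test sentence with a statement to this effect: continuous outcomes, including the primary outcome, will be compared between arms by ANCOVA with the baseline value of that outcome as covariate; the adjusted mean difference and its 95% CI will be reported, and the t test on change will be a supportive analysis. Include site as a covariate only if randomization is stratified by site.

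With baseline in the model, the treatment estimate is the same whether week-12 weight or change is the response, so the wording about body weight and BMI no longer needs interpretation. Absolute weight and BMI can be entered either way; percent change takes baseline weight as its covariate.

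The cost is one sentence and one degree of freedom. No new data are needed.
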